#### Cognitive task

3.3.1

The cognitive task is based on that developed by Hassan et al. (2024). It consists of a battery of four different cognitive tasks, each designed to challenge a different aspect of executive function: A‐X Continuous Performance Test (CPT), n‐back, mental rotation task, and visual search task. The AX‐CPT was chosen as the task in which to measure task performance, and therefore it will be presented first and last as in Hassan et al. (2024). The remaining tasks were presented in a pseudorandom order as designed in Hassan et al. (2024), where the tasks did not repeat back‐to‐back; the time between tasks being repeated was maximized; and the time between tasks being repeated was similar between the different tasks, so that if any order effect was present, it would be the same for all participants.

In the original study (Hassan et al., 2024), each cognitive task was performed for 10 min at a time and was repeated three times, resulting in a total duration of 2 h (four tasks × 10 min per task × three repeats = 4 × 10 min × 3 = 120 min). In the present study we will reduce the duration of each task to 2 min, giving a total duration of 24 min (four tasks × 2 min per task × three repeats = 4 × 2 min × 3 = 24 min). This has been done in consultation with our patient and public involvement group to avoid placing excessive burden on a population that reports high fatigue levels. The modified duration is expected to induce fatigue as participants are required to task switch between multiple short‐duration tasks, constituting an additional demand that increases cognitive fatigue (Dang et al., 2013). Testing of this modified task in 15 young healthy individuals indicates a significant increase in fatigue from pre‐ to post‐task. Fatigue measured on a 100 mm visual analogue scale (VAS) increased from a mean (standard error) of 26 (5) mm pre‐task to 59 (5) mm post‐task (Student's paired *t*‐test *t* = −7.251; *P* < 0.001). Fatigue measured using the fatigue subscale of the Brunel Mood Scale increased from a median (interquartile range) of 7.0 (1.5) pre‐task to 9.0 (4.0) post‐task (Wilcoxon signed rank test *Z* = 2.991; *P* = 0.003) ([name] and [name], unpublished data; Figures 3 and 4). Participants will be sent a training version of this protocol prior to attending the lab session, and this will allow them to familiarize themselves with the tasks involved to minimize any learning effect during the testing session. The cognitive task will be completed on a computer that will be placed in front of participants. Full details of the task are in Supporting information, Appendix 2.

**FIGURE 3 eph13615-fig-0003:**
[figure not shown]
VAS‐F scores. (a) Before and after completing the cognitive fatigue task battery. Black circles represent the mean score. Error bars show ±1 standard error. Light grey lines show individual scores. (b) Difference before and after completing the cognitive fatigue task battery. Values above the dotted line represent an increase in fatigue. Statistical significance shown: ****P *< 0.001. Unpublished data from [name] and [name] (2024).

**FIGURE 4 eph13615-fig-0004:**
[figure not shown]
BRUMS fatigue scores. (a) Before and after completing the cognitive fatigue task battery. Black circles represent the mean score. Error bars show ±1 standard error. Light grey lines show individual scores. (b) Difference before and after completing the cognitive fatigue task battery. Values above the dotted line represent an increase in fatigue. Statistical significance shown: **P *< 0.05. Unpublished data from [name] and [name] (2024).

#### Physical task

3.3.2

The physical task is the 6‐minute walk task (6MWT). This requires participants to walk at their fastest pace for 6 min, aiming to cover as much ground as possible. Participants are able to take breaks at any point, with the clock continuously running (American Thoracic Society, 2002).

The test will be carried out on a self‐paced treadmill (Motek Medical). Four retroreflective markers will be placed on the pelvis over the left and right anterior and posterior superior iliac spines. The position of these markers will be recorded by a three‐dimensional optoelectronic motion capture system (Vicon Nexus, Oxford, UK) and streamed in real time into D‐flow software version 3.36.2 (Motek Medical). D‐flow software will monitor the position of these markers and control treadmill speed according to the position of the participant. This allows the participant to walk on the treadmill at a fluctuating speed, including slowing to a stop for rests whenever they want. The speed of the treadmill belt and the distance covered will be recorded within D‐flow software. Participants will be fitted with a security harness and will be allowed to familiarize themselves with the self‐paced treadmill for up to 5 min prior to the start of the physical task. Participants will be allowed to hold onto the siderails for stability.

The 6MWT induced fatigue in individuals with multiple sclerosis (McLoughlin et al., 2016), indicating it is an appropriate task to induce fatigue in long COVID participants. It is not anticipated that this task will cause significant fatigue in healthy (control) participants. However, healthy (control) participants will be asked to perform the task to provide control data and inform interpretation of data from participants with long COVID fatigue.

### Outcome measures

3.4

#### Participant characteristics

3.4.1

Participant characteristics (age, sex, ethnicity) will be captured using a custom form (Supporting information, Appendix 1). Trait fatigue (severity and impact), emotional symptoms, illness beliefs, and autonomic nervous system symptoms will be evaluated using the validated measures outlined below. This will allow appropriate descriptive reporting of the characteristics of the study sample and will also be used in exploratory analyses to develop future hypotheses (Research Question 4).

The severity of trait fatigue will be evaluated using the Fatigue Assessment Scale (FAS) and the Chalder Fatigue Questionnaire (CFQ‐11). The impact of fatigue will be evaluated using the Modified Fatigue Impact Scale (MFIS). The FAS is a validated unidimensional measure of fatigue that evaluates fatigue severity (Michielsen et al., 2003). The FAS consists of 10 items, each on a 5‐point rating scale, with total score ranging from 10 to 50. The FAS provides one unidimensional score for fatigue, with higher scores indicating greater fatigue severity. This measure is recommended as a core outcome measure for long COVID fatigue (Gorst et al., 2023), and inclusion will allow for comparison across long COVID research. The CFQ‐11 (Chalder et al., 1993) and MFIS (Ritvo et al., 1997) are multidimensional measures that provide individual scores for individual dimensions of fatigue. The CFQ‐11 consists of 11 items, each on a 3‐point Likert scale. The CFQ‐11 produces two individual scores of mental and physical fatigue. The MFIS consists of 21 items, which provide three individual scores of the perceived impact of physical, cognitive and psychosocial fatigue.

Self‐reported autonomic system function will be evaluated using the Composite Autonomic Symptom Score‐31 (COMPASS‐31) scale, which evaluates neurodegenerative system symptoms through 31 patient‐reported questions (Sletten et al., 2012). Assessment is through six weighted domains: orthostatic intolerance (10 points), vasomotor (6 points), secretomotor (7 points), gastrointestinal (28 points), bladder (9 points) and pupillomotor (15 points). A higher score indicates higher severity of autonomic dysfunction. The COMPASS‐31 scale has been used to measure autonomic dysfunction in long COVID populations. A large survey of individuals with long COVID found that 66% of patients were classified as having moderate to severe autonomic dysfunction quantified as a COMPASS‐31 score of ≥20 (Larsen et al., 2022).

Mood will be evaluated using the Hospital Anxiety and Depression Scale (HADS) (Zigmond & Snaith, 1983), which is a reliable and valid measure for assessing anxiety and depression (Herrmann, 1997). The HADS comprises 14 items, seven relating to anxiety and seven to depression. Items are rated on a 4‐point rating scale and produce two scores, one for anxiety (HADS‐A) and one for depression (HADS‐D). Scores can be interpreted as non‐cases (<7), mild (8–10), moderate (11–14) and severe (15–21) symptoms (Zigmond & Snaith, 1983).

Illness beliefs will be evaluated using the Brief Illness Perception Questionnaire (B‐IPQ) (Broadbent et al., 2006). The B‐IPQ is an eight‐item questionnaire that assesses cognitive illness representations, emotional illness representations, and illness coherence representation. The B‐IPQ has evidence of test–retest reliability and concurrent and discriminant validity (Broadbent et al., 2006). Each item is rated on a 0−10 scale, with higher scores indicating a more threatening perception of the illness. The total score is calculated by summing the scores of all eight items, with a possible range of 0–80. Higher scores indicate distorted or unhelpful illness beliefs.

#### State fatigue

3.4.2

State fatigue will be evaluated using a 100 mm VAS that asks participants to rate their current level of fatigue. The VAS will be anchored on the left side with ‘not fatigued at all’ and on the right side with ‘extremely fatigued’ (Supporting information, Appendix 3).

Participants will be asked to make a line on a paper copy of the VAS at six time points across each testing session: at baseline (BL), immediately after the pre‐task somatosensory gating measure (PRE‐1), immediately after the pre‐task somatosensory attenuation measure (PRE‐2), immediately after the completion of the task (cognitive or physical) (POST‐1), immediately after the post‐task somatosensory gating measure (POST‐2), and immediately after the post‐task somatosensory attenuation measure (POST‐3) (Table 1 and Figure 2). This is to allow evaluation of the time course of fatigue and recovery of fatigue over the period required for the outcome measures. State fatigue at each time point will be quantified as the distance of the mark made by the participant from the left‐edge of the horizontal line (range 0−100 mm).

**TABLE 1 eph13615-tbl-0001:** Outcome measures.

		Time point of measurement		
Concept	Measure	Prior to first testing session	Cognitive task testing session	Physical task testing session
Severity of trait fatigue	FAS CFQ‐11 total CFQ‐11 physical subscale CFQ‐11 mental subscale	Prior to session		
Impact of trait fatigue	MFIS physical subscale MFIS cognitive subscale MFIS psychosocial subscale	Prior to session		
Autonomic symptoms	COMPASS‐31	Prior to session		
Mood	HADS‐A HADS‐D	Prior to session		
Illness beliefs	BIPQ	Prior to session		
Autonomic function	HRV		During somatosensory attenuation measure and throughout cognitive and physical task	During somatosensory attenuation measure and throughout cognitive and physical task
State fatigue	Visual analogue scale		BL, PRE‐1, PRE‐2, POST‐1, POST‐2, POST‐3	BL, PRE‐1, PRE‐2, POST‐1, POST‐2, POST‐3
State fatigue	Numeric rating scale		After every fourth task and at the end of the cognitive task	90 s, 180 s and 270 s and at the end of the 6MWT
Perceived effort	Rating of perceived exertion scale		After every fourth task and at the end of the cognitive task	90 s, 180 s and 270 s and at the end of the 6MWT
Cognitive fatigability	BIS		During cognitive task	
Physical fatigability	Average walking speed from 330 to 360 s of 6MWT minus average walking speed from 30 s to 60 s			During physical task
Somatosensory attenuation	Mean force overcompensation at each target force Intercept and slope from a linear regression of matched versus target force		Pre‐ and post‐task	Pre‐ and post‐task
Somatosensory gating	*I* _50_rest_ − *I* _50_movement_		Pre‐ and post‐task	Pre‐ and post‐task

Abbreviations: BIPQ, Brief Illness Perception Questionnaire; BIS, Balanced Integration Score; BL, Baseline; CFQ‐11, Chalder Fatigue Questionnaire; COMPASS‐31, Composite Autonomic Symptom Score; FAS, Fatigue Assessment Scale; HADS‐A, Hospital Anxiety and Depression Scale anxiety subscale; HADS‐D, Hospital Anxiety and Depression Scale depression subscale; HRV, heart rate variability; MFIS, Modified Fatigue Impact Scale; POST‐1, immediately after the completion of the task (cognitive or physical); POST‐2, immediately after the post‐task somatosensory attenuation measure; POST‐3, immediately after the post‐task somatosensory gating measure; PRE‐1, immediately after pre‐task somatosensory attenuation measure; PRE‐2, immediately after pre‐task somatosensory gating measure.

In addition, state fatigue will be reported using a numerical rating scale (NRS) at four time point during the physical and cognitive tasks. This will be at 90, 180 and 270 s of the 6MWT and after every fourth task in the cognitive task and at the end of each task. In the cognitive task these ratings will be time stamped. Participants will be shown the NRS, which consists of a scale from 0 to 10, with 0 being anchored as ‘not fatigued at all’ and 10 being anchored as ‘extremely fatigued’. They will be asked to verbally report the number that corresponds to their fatigue level. The need to switch from a VAS to an NRS is dictated by the inability of participants to physically mark a line on a piece of paper while completing the 6MWT.

#### Perceived effort

3.4.3

Perceived effort will be evaluated using the Borg rating of perceived exertion (RPE) scale. This requires participants to rate how much effort an activity takes on a scale of 6 (no exertion at all) to 20 (maximal exertion). RPE will be measured at the same time points as the NRS. Participants will be shown the RPE scale prior to carrying out the tasks, as done in previous studies where participants were asked to report their RPE during a task (Flairty & Scheadler, 2020). This will allow us to make distinctions between perceived effort and fatigue during exertion. Participants will be shown the RPE scale during each task, and will be asked to verbally report the number that corresponds to their level of exertion.

#### Autonomic nervous system function

3.4.4

Autonomic nervous system function will be quantified using heart rate variability (HRV), calculated as the proportion of successive intervals which differ by >50 ms (Baker et al., 2023). Heart rate will be measured using a polar H10 Hartslagsensor (Polar) streamed into Dflow software (Motek Medical). HRV will be measured during the somatosensory attenuation measure to ensure that participants are sitting quietly, not engaged in trial activity. This will replicate previous measurement in individuals with long COVID to allow comparison (Baker et al., 2023). HRV will additionally be measured throughout the cognitive and physical tasks to allow exploratory analysis of the change in autonomic nervous system function during exertion. HRV measured over a short period mostly reflects parasympathetic nervous system activity (Gullett et al., 2023). HRV has been used as a measure of autonomic nervous system function to quantify autonomic function changes in response to various interventions (Ali & Chen, 2023). Example code used to calculate HRV is provided as Supporting information.

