#### Planned exploratory analysis

3.7.1

Hypotheses 1, 2, 3 will be rerun with age included as a covariate.Hypotheses 1, 2, 3, 4 will be rerun with time of day (morning/afternoon) at which participants completed sessions and session order (cognitive/physical first) included as additional predictor variables.The effect of autonomic dysfunction during exertion, on state fatigue pre‐ to post‐exertion, via an effect on somatosensory processing post‐exertion will be tested using mediation analysis with separate models for somatosensory attenuation and somatosensory gating. This will be quantified in participants with and without long COVID.The relations between autonomic dysfunction during exertion, state fatigue during exertion, and perceived effort during exertion will be quantified in participants with and without long COVID during both tasks (cognitive/physical). This will be tested using correlation analysis.Test‐retest reliability will be conducted for each somatosensory processing measure (gating and attenuation), from the baseline measure from each session (cognitive/physical). This will provide a measure of whether somatosensory processing is stable over time.

We will carry out outcome neutral criteria that must be met for successful testing of the stated hypothesis. This includes checking for the absence of floor or ceiling effects. This will be done by examining data distributions to ensure that there are no extreme values that could impact the validity of results. Additionally, we will investigate the quality of the data and this will include frequency measures and the shape of the distribution.

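### During the 6-minute walk the 50 ms heart-rate-variability proportion is at risk of a floor effect, and the plan names no alternative index for the physical-task part of the exploratory exertion analyses

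*Protocol article*

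**What the plan says.** Section 3.4.4 of the protocol article defines heart rate variability (HRV) as "calculated as the proportion of successive intervals which differ by >50 ms". Table 1 lists only HRV under autonomic function, and no second index is named. Comparability with earlier long COVID data is given as a reason only for the recording made in quiet sitting. For the tasks the article says: "HRV will additionally be measured throughout the cognitive and physical tasks to allow exploratory analysis of the change in autonomic nervous system function during exertion". It also notes: "HRV measured over a short period mostly reflects parasympathetic nervous system activity".

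The two tasks differ greatly in physical demand. Of the walk, section 3.3.2 says: "This requires participants to walk at their fastest pace for 6 min". It adds: "Participants are able to take breaks at any point, with the clock continuously running". The other task is done at a computer, with shortened blocks "giving a total duration of 24 min" (section 3.3.1).

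Section 3.7.1 plans a mediation analysis with autonomic dysfunction during exertion as the exposure; it does not say for which task. It also plans correlations, in both groups and both tasks, for "The relations between autonomic dysfunction during exertion, state fatigue during exertion, and perceived effort during exertion". The same section requires a check that floor and ceiling effects are absent, without saying what follows if HRV fails it.

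**The concern.** An index that counts differences above a fixed 50 ms threshold loses information once most differences fall well below it: participants with different beat-to-beat variability all score zero. The article itself ties the index to parasympathetic activity. If that activity falls in a fastest-pace walk and intervals shorten, the threshold becomes harder to reach. At an assumed 120 beats/min the mean interval is 60,000/120 = 500 ms, so 50 ms is 10% of it. At 75 beats/min the interval is 800 ms and 50 ms is 6.25%.

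Two consequences follow if walkers cluster at zero. A weak correlation or absent mediation in the walk could be read as no link between autonomic function and fatigue. And if the computer task leaves the index off its floor, a relation seen there but not in the walk could come from the measure rather than from physiology.

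**Working it through.** **Plan's own figure.** There is none to reproduce. The article gives no heart rate, RMSSD or 50 ms proportion, at rest or in either task. All values of these below are assumptions, shown as a range.

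**Step 1: the index as a function of beat-to-beat variability.** Let successive differences be normal with mean zero and SD s, so that RMSSD = s. Then

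proportion = 2 × (1 − Φ(50/s)).

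| s (ms) | 50/s | Proportion above 50 ms |
|---|---|---|
| 40 | 1.25 | 21.1% |
| 30 | 1.67 | 9.6% |
| 20 | 2.50 | 1.2% |
| 15 | 3.33 | 0.09% |
| 10 | 5.00 | about 0.0001% |

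Over 6 minutes at an assumed 120 beats/min there are 720 beats. The expected number of qualifying intervals is 720 × 0.0124 ≈ 9 at s = 20 ms, 720 × 0.00086 ≈ 0.6 at 15 ms, and about 0.0004 at 10 ms.

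**Step 2: spread between people.** People differ in s, so RMSSD was simulated as log-normal between participants (SD of the log 0.4 to 0.6), with binomial counting over the beats in each task. Ranges are over the three log-SDs.

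| Task, assumed median RMSSD, heart rate | Exactly 0 | Below 1% | SD (points) | Correlation of index with log RMSSD |
|---|---|---|---|---|
| Walk, 6 ms, 130/min | 93–99% | 97–100% | 0.2–1.3 | 0.16–0.31 |
| Walk, 10 ms, 120/min | 74–84% | 87–95% | 1.1–4.0 | 0.43–0.53 |
| Walk, 15 ms, 110/min | 50–51% | 66–74% | 3.7–8.4 | 0.67–0.71 |
| Walk, 20 ms, 105/min | 26–33% | 48–49% | 7.1–12.2 | 0.81 |
| Cognitive, 25 ms, 80/min | 7–16% | 27–33% | 10.1–15.6 | 0.88–0.89 |
| Cognitive, 40 ms, 75/min | 0–4% | 3–11% | 15.6–20.9 | 0.96–0.98 |

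In a group of 44, the mildest walk row puts about 44 × 0.26 ≈ 11 to 44 × 0.33 ≈ 15 people at exactly zero. The 10 ms row puts 44 × 0.74 ≈ 33 to 44 × 0.84 ≈ 37 there. The cognitive task stays largely clear over 25 to 40 ms; that too is an assumption, since at a median of 20 ms 19–28% would be at zero.

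**Step 3: what this does to a correlation.** Suppose fatigue is linearly related to log RMSSD with the same true correlation, say 0.40, in both tasks, and to the index only through log RMSSD. The expected correlation with the index is then 0.40 times the last column:

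- walk at 10 ms: 0.40 × 0.43 = 0.17 to 0.40 × 0.53 = 0.21;
- cognitive task at 25 ms: 0.40 × 0.88 = 0.35 to 0.40 × 0.89 = 0.36.

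Equal physiology would thus look about twice as strong in the cognitive task. At a walking median of 20 ms the figure is 0.40 × 0.81 = 0.32, and the contrast nearly vanishes. Using ranks of the index recovers part of the loss: at 10 ms the ranks correlate 0.66–0.75 with log RMSSD, giving 0.26 to 0.30.

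**The case against.** The strongest reply is that the deciding fact is missing. Nothing in the article shows how far beat-to-beat variability falls in this walk. At a median of 15 to 20 ms the index still has an SD of roughly 4 to 12 points. The treadmill is self-paced and breaks are allowed, so intensity will differ between people and some will keep non-zero values. This stands: a reader might infer that the index drops to about zero in the walk, or that any remaining values are movement artefact, and the document supports neither.

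A reader might also infer that the exertion analyses as a whole have almost no predictor variation. They do not: the correlations also cover a 24-minute computer task, where no floor follows over the assumed 25 to 40 ms.

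Two further replies carry less weight. First, the analysis might use the change from sitting rather than the level in the walk. But if the walking value is near zero, the change is close to minus the seated value, so the variable would mostly restate the resting measure. Second, a floor check is planned. It should reveal the problem, but the article states neither an action nor a substitute index. Because a Stage 2 registered report is to follow (section 3.9), an index chosen after seeing the data would be a deviation. The supporting HRV code is not shown and might compute more; the article text fixes only the one index.

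Finally, these analyses are exploratory. That is right, and it limits the weight of the point.

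**Conclusion.** The point holds as a risk confined to the 6-minute walk. Under normal successive differences and an assumed median walking RMSSD of 20 down to 6 ms, between about a quarter and nearly all participants would score exactly zero. The physical-task part of the exploratory mediation and correlation analyses would be weakened, slightly at the upper end of that range and severely at the lower. A difference between tasks could then be an artefact of the index. Whether this happens depends on variability during the walk, which the document does not report.

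Nothing here touches Research Question 1, the sample size of 44 per group, or the seated HRV measure. Research Question 4 is not shown to use HRV from the tasks, since section 3.4.4 assigns those recordings to exploratory analysis. The change is worth making because it costs almost nothing, not because the main conclusions depend on it.

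**What to change.** In sections 3.4.4 and 3.7.1, state that the during-exertion analyses use, in both tasks, log RMSSD after artefact correction, plus the rise in mean heart rate from the seated period. Both come from the recording already planned. Keep the 50 ms proportion for the seated measure, where it allows comparison with earlier long COVID data. Say that the floor check applies to the HRV variables, and what will be reported if a variable fails it.

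Adjustment for walking speed in the physical task should be at most a sensitivity analysis: speed may itself be a consequence of fatigue, so adjusting for it could remove part of the relation under study.

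The cost is a few lines of code and wording, with no new data and no added burden on participants. The downside is that exertion and seated indices would not be directly comparable; reporting log RMSSD for the seated period as well removes it.
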